**Regular health care**		
regular GP contacts	X	electronic health record
out-of-office hours GP contacts	X	-
home care	X	home care organization
domestic care	X	municipality
medication	X	electronic health record
residential home admissions	X	-
nursing home admissions	X	-
day care in residential home	X	-
day care in nursing home	X	-
hospital admissions	X	-
physiotherapist	X	-
assistive devices	X	-
**CareWell-primary care program**		
time needed for proactive care planning / case management / multidisciplinary deliberation medication review	-	time registrations by health care professionals

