[14,15]. Furthermore, previous studies have shown some cost-saving implications through a postponement or reduction in residential or nursing home admissions, hospital admissions and emergency department visits
[11,13,16-18].

The CareWell-primary care program is a complex intervention integrating cure, care and welfare, that aims to prevent functional decline, improve quality of life and reduce or postpone hospital admissions and nursing home admissions in community-dwelling frail elderly. The program is based on existing chronic care models and is adapted to the Dutch health care system. It is designed as part of the National Care for the Elderly Program, which is launched in 2008 by the Netherlands Organization for Health Research and Development (ZonMW), in cooperation with the Nijmegen Network for the Care and Welfare of Elderly People
[4]. In developing the program, both health care professionals and a panel representing frail elderly and their informal caregivers were closely involved.

Complex interventions comprise multiple components that are interrelated or interdependent and therefore can be difficult to develop, document, evaluate and reproduce
[19]. To create a better understanding of how and why a complex intervention works, and to gain insight into costs and benefits, the framework for development and evaluation of complex interventions as published by the UK Medical Research Council is widely used
[20]. This framework emphasizes the value of including a process evaluation and an economic evaluation alongside the outcome evaluation. It provided the theoretical background for the design of our study. By gaining process information, we aim to detect gaps in implementation that might be responsible for the effectiveness of the program. Furthermore, we will explore why some general practices are more successful than others in improving the quality of care for their frail elderly patients
[21].

This paper presents the elements of the CareWell-primary care program as well as the design of both the CareWell-primary care (cost-) effectiveness study and process evaluation.

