### Study population

#### Recruitment of general practices

General practitioners (GPs) are recruited to participate in the CareWell-primary care program through an invitational letter and a subsequent telephone call from one of the principal investigators. They are fully informed on the EasyCare Two-step Older persons Screening instrument (EasyCare-TOS)
[23], used to identify the frail elderly study participants, and on the elements of the program. GPs with a minimum of 300 patients aged 70 years or above in their practice population, a solid motivation to implement the program, and the organizational facilities required for implementation are eligible to participate in the intervention arm. After their informed consent, six GPs will be non-randomly assigned to the intervention arm.

A second group of GPs is similarly recruited to participate in the control group. These GPs receive information on the EasyCare-TOS, but no information on the CareWell-primary care program in order to prevent contamination bias. Furthermore, they are explicitly instructed to deliver ‘care as usual’, and not to start new collaborations with community nurses, elderly care physicians or gerontological social workers. No restrictions on existing collaborations are imposed. However, no multidisciplinary team collaborations comparable to those in the CareWell-primary care program are regularly available in usual care. Six GPs consenting to participation are non-randomly assigned to the control arm.

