**Figure 1 F1:**
[figure not shown]
Schematic representation of the EasyCare-TOS and the elements of the CareWell-primary care program.

The program consists of four key elements: (1) multidisciplinary team work, (2) proactive care planning, (3) case management, and (4) medication reviews. Each general practice will assemble one or two multidisciplinary teams, consisting of the GP, the community nurse, an elderly care physician and a gerontological social worker. These team members closely collaborate to ensure integration of cure, care and welfare. Face-to-face multidisciplinary team meetings will be held at least twice a year for each frail elder, in which care plans will be reviewed and adapted. In addition, the team members will be able to virtually communicate at all times within a secured web based health and welfare information portal (ZWIP)
[24]. This portal combines a shared Electronic Health Record with a communication tool for primary care professionals, which is accessible to all involved caregivers through a secured login procedure.

A proactive integrated care plan is formulated for each participant on enrollment in the program. These care plans will be based on the individual patients’ health-related goals and needs on the domains of cure, care and welfare as obtained with the EasyCare-TOS. The care plans will be stored in the ZWIP.

All elders will be assigned a case manager. This will be either the community nurse or the gerontological social worker, depending on the nature of the participants’ health-related needs. The case manager will be responsible for the organization of the multidisciplinary team meetings and for the coordination and monitoring of the proactive care process according to the care plan, as directed by the primary care physician. Moreover, the case manager will provide participant-support in goal setting and self-management by means of home-visits and telephone contacts.

The GP, community nurse and pharmacist will conduct a yearly medication review for those elders using five or more drugs for chronic use. Agreements on discontinuing inappropriate or unnecessary medications and starting medications in case of under-treatment will be incorporated in the care plan, thus ensuring appropriate drug treatment
[25].

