#### Economic evaluation

The economic evaluation will be conducted from a societal perspective. All relevant direct and indirect costs per participant will be determined by considering costs of the CareWell-primary care program, for the intervention group, and regular health care costs, for both the intervention and the control group. The costs of the CareWell-primary care program will be calculated from the registrations of health care professionals of the time spent on the elements of the program. Regular health care costs will be collected with EasyCare-TOS and external sources, as shown in Table 
1.

Unit resource prices are based on guideline prices according to the Dutch Insurance Board
[35]. Real costs prices will be determined when unit resource prices are not available. Societal costs are quantified by calculating productivity losses for informal caregivers who perform paid labor during the study period using the friction cost method
[36]. Data on productivity losses will be obtained using the structured caregiver questionnaires.

The incremental cost-effectiveness ratio (ICER) will be expressed as costs per quality-adjusted life years (QALYs) gained, as measured with the Euroqol-5D
[30]. From these EQ-5D scores, utilities will be derived using the trapezium rule and the Dutch algorithm after which QALYs will be calculated
[37].

Next to this, the ICER will be expressed as the difference in total mean costs weighed against the difference in the sum-scores between baseline and follow-up on functional performance, as measured with the Katz-15 index
[28].

Both ICERs are subjected to bootstrap analysis and will be presented in cost-effectiveness planes. Deterministic uncertainty will be explored on a range of extremes of parameters potentially influencing the ICERs, i.e. sensitivity analyses. Furthermore, stochastic uncertainty surrounding the ICERs will be presented using a cost-effectiveness acceptability curve.

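### Table 1 has no regular-care item for elderly care physician, social worker, emergency department or outpatient specialist contacts, so the cost difference behind both ICERs is open to bias

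*Protocol article*

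**What the plan says.** In the protocol article, Outcome measures and data collection (cost-effectiveness study) and Economic evaluation both point to Table 1 for how costs are obtained. The table has two blocks.

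- **Regular health care**, 12 rows: GP contacts (regular and out of hours), home care, domestic care, medication, residential home and nursing home admissions, day care in each of these settings, hospital admissions, physiotherapist and assistive devices. All come from the EasyCare-TOS, some with an external source as well.
- **The programme**, one row covering care planning, case management, team deliberation and medication review. Its only source is "time registrations by health care professionals".

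Economic evaluation takes a societal perspective, undertakes to determine every relevant cost, and builds the total from "costs of the CareWell-primary care program, for the intervention group, and regular health care costs, for both the intervention and the control group". Programme cost is "calculated from the registrations of health care professionals of the time spent on the elements of the program".

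The programme team is described as "consisting of the GP, the community nurse, an elderly care physician and a gerontological social worker". Of control practices, Recruitment of general practices says: "No restrictions on existing collaborations are imposed". The supporting elements of the intervention include ready access to a geriatrician or geriatric psychiatrist, and agreements on hospital admission and discharge. Background lists "hospital admissions and emergency department visits" among the places where earlier studies of such care models found savings.

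**The concern.** An incremental cost is credible only if the same kinds of care are recorded in the same way in both arms. Here, two of the four team disciplines generate cost in the intervention arm through the programme row. Any contact with them outside the programme, which in the control arm means any contact at all, has no row. Emergency and outpatient specialist visits have no row in either arm, although the programme is designed to alter how participants reach specialists and hospital.

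A cost component that was never recorded cannot be recovered by a later analysis plan. Both ICERs (per QALY and per unit of Katz-15 change), the cost-effectiveness planes and the acceptability curve use this cost difference. The Discussion intends the results to inform nationwide implementation and structural financing.

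A lesser matter is allocation. The article says "the case manager will provide participant-support in goal setting and self-management by means of home-visits and telephone contacts". Where the case manager is a community nurse, such a visit could be entered as programme time and also appear in home-care records. A GP contact made for the programme could likewise appear in the electronic health record. The article does not say how such a contact is assigned.

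**Working it through.** The plan states no cost, unit price, contact rate or ICER, so there is no figure to reproduce. The check is a comparison of coverage, followed by the sign of any error.

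**Step 1. Coverage in Table 1, by arm**

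| Resource | Intervention arm | Control arm |
|---|---|---|
| Elderly care physician, within programme | time registration | not applicable |
| Elderly care physician, outside programme | no row | no row |
| Social worker, within programme | time registration | not applicable |
| Social worker, outside programme | no row | no row |
| Emergency department visit | no row | no row |
| Outpatient specialist visit | no row | no row |
| GP contact | regular rows; programme row if registered | regular rows |
| Community nurse contact | home care row if recorded there; programme row if registered | home care row if recorded there |

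The nearest rows to an emergency visit are out-of-hours GP contacts and hospital admissions; neither is an emergency department visit. Specialist consultation is not among the activities named in the programme row either.

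**Step 2. Sign of the error**

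Per participant, let:

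- P = programme cost
- R = regular cost that Table 1 records
- U = cost of the two professions outside the programme
- E = emergency and outpatient specialist cost
- d = programme time also counted in a regular row

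Subscripts I and C denote the arms.

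- True difference = (P + R_I + U_I + E_I) − (R_C + U_C + E_C)
- Measured difference = (P + R_I + d) − R_C
- Bias = measured − true = c + d − e, where c = U_C − U_I and e = E_I − E_C

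It follows that:

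- If c = 0, d = 0 and e = 0, the bias is 0.
- If c > 0 (more unrecorded use in controls), the incremental cost is overstated. If c < 0, it is understated.
- If d > 0, it is overstated.
- If e < 0 (the programme lowers emergency and specialist use), it is overstated. If e > 0, it is understated.

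**Step 3. Illustration, all inputs assumed**

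Take c and d each as 0, 50 or 200 euro and e as −100, 0 or +100 euro per participant.

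- Lowest: 0 + 0 − 100 = −100 euro
- Highest: 200 + 200 − (−100) = +500 euro
- Omissions alone (d = 0): from 0 − 100 = −100 to 200 + 100 = +300 euro
- Offsetting case: 50 + 50 − 100 = 0 euro

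**Step 4. Effect on the cost per QALY**

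The ICER shifts by bias ÷ QALY gain. The documents give no expected gain. At an assumed 0.025, 50 euro shifts it by 50 ÷ 0.025 = 2,000 euro per QALY. Doubling the gain halves this shift, and halving the gain doubles it. This shows sensitivity only; it is not an estimate.

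**The case against.** Several points on the other side stand.

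- **Control-arm use may be small.** Leaving existing collaborations unrestricted does not show that any exist with these disciplines. The same section says comparable team collaborations are not regularly available in usual care, and bars control GPs from starting new ones with these professionals. Elders already in a comparable case-management programme are excluded. This limits the size of c but does not make individual contacts zero.
- **The gap is shown for Table 1 only.** The article says that service-use data are embedded in the EasyCare-TOS, and its step 2 questionnaire is an additional file that is not shown. A reader might infer that emergency visits are recorded nowhere; the documents do not establish that.
- **Emergency visits are not a stated target.** Background cites them from earlier studies of other programmes. Hospital and nursing home admissions, which this programme does aim to reduce, are both in the table. An omission common to both arms matters only if use differs between them.
- **Double counting is not shown.** The headings separate regular from programme care, and programme cost is limited to programme elements, so a split seems intended. The operating rule may sit in the full protocol. Social worker case managers cannot be double counted, because no regular row covers them.

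The planned deterministic sensitivity analyses are a partial answer: they can vary an assumed value for unrecorded use but cannot supply the data.

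**Conclusion.** The point holds as a gap in cost measurement. As written, Table 1 falls short of the scope that Economic evaluation claims, and it leaves the cost difference behind both ICERs open to bias. Net unmeasured control-arm use of the elderly care physician and social worker would overstate the programme's incremental cost. For emergency and specialist visits the direction is uncertain: better coordination could lower this use, and easier specialist access could raise it.

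A reader might go further and conclude that the cost difference is biased, or put a euro figure on it. The documents support neither. The bias is zero under conditions that they do not rule out, and every price, contact count and QALY gain in the illustration is assumed.

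The conclusion rests on Table 1 being the complete list of utilisation items. If the questionnaire already holds the missing ones in both arms, only the table and the allocation statement need correcting. The primary Katz-15 comparison is unaffected. This is an inexpensive improvement to the economic evaluation.

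**What to change.** 1. Add to Table 1, and to the EasyCare-TOS utilisation items unless already there, with identical wording in both arms: emergency department visits, outpatient specialist visits, and contacts with an elderly care physician or a social worker outside the programme.
2. State that each contact is costed once: a GP or community nurse contact registered as programme time is not also costed as a regular GP contact or as home care.

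A written allocation rule is enough for the second item. Matching records by professional and date would need dated, participant-level entries. The article does not say that the time registrations have these, and the EasyCare-TOS is administered only at baseline and twelve months.

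The cost is a few more questions in an interview already held in both arms, some recall error on the new items, and one sentence on allocation.

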#### Sample size calculation

The change in functional status between baseline and follow-up will be measured as a change in the sum-score on the Katz-15 index between baseline and 12 months
[28]. Although the Katz-15 index scores may be skewed, we expect these sum-score differences to have a normal distribution. For financial and logistic reasons, including 6 clusters in each study-arm is thought to be feasible. Each general practice is instructed to include 50 frail elderly. Based on the assumptions that 15% of eligible elders will decline informed consent and 20% will be lost to follow-up within the intervention-period of twelve months, the expected cluster size is 35. Using a two-sided alpha of 0,05, a power of 80%, an assumed between-clusters ICC of 0,01
[32], and a minimum cluster size of 35 with 2×6 clusters, we will be able to detect an effect size of >0,32, which is sufficient to detect even small differences
[33,34].

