#### Study participants in the cost-effectiveness study

In each general practice, a random sample of fifty frail elders aged 70 years or above will be included in alphabetical order with the use of the EasyCare-TOS screening instrument
[23]. In step 1 of the EasyCare-TOS, the GP rapidly subdivides ‘not-frail’ from ‘(possibly-) frail’ elders by using prior, tacit knowledge. (Possible) Frail elders proceed to step 2, in which a trained community nurse or research assistant conducts a comprehensive geriatric assessment during a home-visit. The EasyCare-TOS step 2 questionnaire is shown in Additional file
1. In both study arms 300 frail elders will be included. Excluded from participation are (1) elders living in a residential or nursing home, (2) critically or terminally ill elders, (3) elders who are already enrolled in a case-management program, comparable to the CareWell-primary care program.

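### The detectable effect of 0.32 at 80% power holds only under a normal approximation; allowing for 12 practices, power is about 72%, and the claim about small differences is not supported

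*Protocol article*

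**What the plan says.** All places are in the protocol article.

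- **Sample size calculation, losses.** "Each general practice is instructed to include 50 frail elderly". It is then assumed that "15% of eligible elders will decline informed consent and 20% will be lost to follow-up within the intervention-period of twelve months", and from this "the expected cluster size is 35".
- **Sample size calculation, power.** The inputs are "Using a two-sided alpha of 0,05, a power of 80%, an assumed between-clusters ICC of 0,01" and "a minimum cluster size of 35 with 2×6 clusters". The conclusion is that "we will be able to detect an effect size of >0,32, which is sufficient to detect even small differences". The effect size is standardised. The article does not say what counts as small, and it does not say whether the calculation allows for the number of practices.
- **Study participants in the cost-effectiveness study.** Fifty frail elders are to be included per practice, and "In both study arms 300 frail elders will be included".
- **Recruitment of general practices** and **Statistical analysis.** The intervention is assigned by practice, six per arm. The analysis is a mixed model with participants nested in practices and correction for relevant covariates.

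**The concern.** The treatment contrast is between practices, and there are only 12 of them. The between-practice variation must be estimated from those 12, so the test has few degrees of freedom and a larger critical value than the normal 1.96. A detectable effect based on normal quantiles is then too favourable.

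Separately, a design that reaches 80% power only at about a third of a standard deviation is presented as able to pick up small differences. A reader who relies on that sentence could take a null result on the Katz-15 as evidence against small effects. Yet the article's own figure already says that effects below 0.32 fall short of 80% power.

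Last, the planning number rests on 50 per practice, and two sections use that 50 differently. If refusals come out of the 50, the article's 300 per arm is not what will be enrolled. If they do not, the analysed cluster size of 35 does not follow. The same 35 is also called expected in one sentence and a minimum in the next, although an expected value is not a floor.

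**Working it through.** **Inputs** (Sample size calculation): two-sided alpha 0.05; power 80%; ICC 0.01; k = 6 practices per arm; m = 35 analysed per practice; effect in SD units, so SD = 1.

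**Formulas.** Design effect DE = 1 + (m − 1) × ICC. Standard error of the arm difference SE = √(2 × DE / (6m)). Detectable effect, normal approximation: (1.960 + 0.842) × SE, that is 2.802 × SE.

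**1. The plan's own figure.**
- m = 35: DE = 1.34; SE = √(2 × 1.34 / 210) = 0.1130; detectable effect 2.802 × 0.1130 = 0.316, which rounds to 0.32. Power at 0.32 is 80.9%.

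So 0.32 reproduces.

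**2. The analysed cluster size.**
- Refusals deducted from the 50: 50 × 0.85 × 0.80 = 34. Enrolled: 50 × 0.85 = 42.5 per practice, or 6 × 42.5 = 255 per arm.
- 50 already consented: 50 × 0.80 = 40 analysed; enrolled 6 × 50 = 300 per arm.

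Neither route gives 35. The step from 34 to 35 is harmless: at m = 34, DE = 1.33, SE = √(2 × 1.33 / 204) = 0.1142, the detectable effect is 0.320 and power at 0.32 is 80.0%. The gap between 255 and 300 enrolled per arm is not a rounding matter.

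**3. Allowing for 12 practices.** The between-practice degrees of freedom are 2 × (6 − 1) = 10, and the two-sided 5% critical value rises from 1.960 to 2.228. Power is the upper tail of a noncentral t on 10 df with noncentrality d/SE. Results for the unadjusted contrast, ICC 0.01:

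| Analysed per practice | SE | d/SE at 0.32 | Power at 0.32, normal | Power at 0.32, 10 df | Detectable at 80%, normal | Detectable at 80%, 10 df |
|---|---|---|---|---|---|---|
| 34 | 0.1142 | 2.802 | 80.0% | 71.5% | 0.320 | 0.355 |
| 35 | 0.1130 | 2.833 | 80.9% | 72.4% | 0.316 | 0.351 |
| 40 | 0.1076 | 2.973 | 84.5% | 76.4% | 0.302 | 0.335 |

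On 10 df, no reading of the enrolment numbers reaches 80% at 0.32. Degrees-of-freedom methods differ, so 10 is the cautious end. At m = 35, 20 df gives 76.9%, 50 df gives 79.3%, and the normal limit is 80.9%.

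**4. Small differences.** The article defines no threshold. Taking 0.20 SD as an assumption, at m = 35 the noncentrality is 0.20 / 0.1130 = 1.770.
- Plan's own method: Φ(1.770 − 1.960) = 42%.
- 10 df: 36%.
- At m = 40 the same steps give 46% and 39%.

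**The case against.** **The figure is right by a standard formula.** This stands. A reader might infer from the list of problems that the planning figures do not reproduce. They do: 0.32 follows from the stated inputs at a cluster size of either 34 or 35. What is missing is an allowance for the small number of clusters, and the article names no reference distribution that this would contradict.

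**The analysis is covariate-adjusted.** The Statistical analysis section says relevant covariates will be corrected for. If they explained about 17% to 19% of the outcome variance (an assumption), the 10-df detectable effect would return to 0.32: (0.32/0.351)² = 0.83 at m = 35 and (0.32/0.355)² = 0.81 at m = 34. But the sample size section claims no such gain, and in a non-randomised comparison adjustment can also cost precision. The point limits how firmly 72% can be stated for the final model. It does not support the printed figure.

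**Small is the authors' term, backed by sources not at hand.** This is fair as far as it goes: 0.20 is an assumed benchmark. The claim remains too strong as worded, because the article's own threshold leaves everything below 0.32 short of 80% power.

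**It may be tempting to say that 50 are only approached.** The documents do not support that as fact. Both sections speak of including 50; only the deduction of refusals suggests a count before consent. If 50 consent, 40 are analysed, and the planning figure of 35 errs on the cautious side.

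**A higher ICC would make matters worse.** That is true in general, but the article gives no basis for a value other than its cited 0.01, and a sensitivity table is not something a condensed article has to carry.

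**Conclusion.** The concern holds in a limited form, and its severity is moderate. The statement of 80% power at 0.32 depends on a normal approximation. For an unadjusted practice-level contrast with ICC 0.01 and 10 df, power at 0.32 is about 72% (71.5% at 34 per practice, 72.4% at 35, 76.4% at 40). The effect detectable with 80% power is then 0.335 to 0.355 SD. At the stated cluster size of 35, a more generous degrees-of-freedom method moves power within 72% to 81%.

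The claim about small differences is unsupported whichever method is used, given 0.20 SD as the assumed meaning of small.

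The two sections conflict on whether 50 per practice and 300 per arm are counted before or after refusals.

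The practical shift is modest, from 0.32 to about 0.35. It does not invalidate the design, and it does not show that the trial needs more patients.

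**What to change.** Changes to text only, in two sections of the protocol article:

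1. State whether 50 per practice is counted before or after refusal of consent, and make the two sections agree. If before, give 34 analysed per practice and about 255 enrolled per arm. If after, give 40 analysed and 300 enrolled. Call the resulting cluster size expected, not minimum.
2. Restate the detectable effect allowing for 12 practices and name the method: about 0.355 SD with 34 analysed or about 0.335 SD with 40, at 80% power, ICC 0.01 and 10 df. If another degrees-of-freedom method or a gain from covariates is intended, say so and give the figure that it yields.
3. Delete the closing clause about small differences. Say instead that effects below about 0.35 SD (about 0.335 if 40 are analysed) are not detectable with 80% power.

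No patients, practices or analyses are added. The only cost is a slightly less favourable stated detectable effect.
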